#### 2.6.5. Plans to Give Access to the Full Protocol, Participant Level-Data and Statistical Code

The study has been registered in an accessible clinical trial register (PACTR202203780981413) and the information contained in that register provides sufficient insight into the full trial design. The final results of the study will be published in peer-reviewed Open Access journals and presented at scientific meetings. None of the trial material may be disclosed to any party not directly involved in the study without written permission from the project partners. Presentation and publication of the trial results will be jointly carried out by the project investigators. Each African collaborator will be in charge of sharing relevant results with their respective health authorities, including the National Malaria Control Programmes. This will be done through ad-hoc meetings, data dissemination workshops, and/or during the celebration of African Malaria Day in each country. Trial data will be accessible for inspection by appropriate health and regulatory authorities.

### 2.7. Oversight and Monitoring

#### 2.7.1. Composition of the Coordinating Center and Trial Steering Committee

The trial is coordinated by a dedicated trial staff based at CRUN (Nanoro, Burkina Faso). CRUN is responsible for generic study protocol development and implementation. Each country is responsible for the ethical review of the study protocol and the implementation of the study at its respective site.

#### 2.7.2. Composition of the Data Monitoring Committee, Its Role and Reporting Structure

CRUN is responsible for the centralized data management and monitoring. The central database will be managed at CRUN by a dedicated data manager, who will run regular consistency checks and produce queries to be resolved by the local investigators. This system will allow the rapid identification of potential problems. Data entry and review will be performed following the Data Management Plan. Data management is independent of the sponsor.

#### 2.7.3. Adverse Event Reporting and Harms

The intervention is unlikely to result in (unexpected) adverse events or harm. This is an ancillary study embedded in the PyraPreg project and the incidental findings policy will follow the one set-up for the PyraPreg project. This study will not involve research conducted on genes and/or the genetic basis of diseases in the human subject. The research is not intended to provide subjects or their families with specific information about their genetic status. Furthermore, the research will be focused on the diagnostic of malaria only (a very common and well-known condition in performance study) and not on any other diseases or conditions and does not actively search for human genetic disorders. Therefore, any other medical problem detected in patients with malaria or those tested negative for these infections will be sent to the nearest health facility for further medical management. The risk that incidental findings occur in this study is very low though it might be the case when blood slides are examined by microscopy, and there is a chance that other parasites, like Trypanosomes or bloodstream microfilariae, will be found. In such a case, the attending physician will be informed to undertake appropriate medical actions.

#### 2.7.4. Frequency and Plans for Auditing Trial Conduct

Each site will be visited by an independent monitor at least once during the conduct of the trial plus a study initiation visit at the start of the study activities and a close-out visit after the last patient has completed the follow up. The task of the Monitor is to verify the best conduct of the study through frequent contacts by phone and in person with the Principal Investigator and site staff, in accordance with applicable regulations, Good Clinical Practice requirements, and study-specific Standard Operating Procedures. The objectives and specific tasks of the Monitor are described in the ICH Guidelines E6. Source documents will be kept for each patient in the study. All information in the electronic CRF must be traceable to these source documents in the patient’s file. The monitor, who is bound by a confidentiality agreement to protect patients’ confidentiality, has access to all relevant source documents to confirm their consistency with the electronic CRF entries.

#### 2.7.5. Plans for Communicating Important Protocol Amendments to Relevant Parties (e.g., Trial Participants, Ethical Committees)

Protocol amendments will be communicated to the sponsor (AMC) and relevant ethical review bodies in the country concerned.

#### 2.7.6. Dissemination Plans

Dissemination of the study findings is planned through scientific papers and conference attendance, and also through meetings with various audiences of interest, including key stakeholders such as public health authorities and diagnostic companies who might be interested in bringing the diagnostic platform to market.

## 3. Discussion

Pregnant women require specific consideration in malaria control programs in endemic countries. Indeed, the increasing susceptibility to malaria infection during pregnancy, makes pregnant women living in endemic areas, an important reservoir of *Plasmodium* in the community [33]. The high susceptibility of pregnant women in many endemic countries interferes with diagnostic testing during pregnancy, rending target interventions ineffective for control [34]. This situation becomes exacerbated when available diagnostics have a low detection limit [6,7,8,9,10] and are unable to detect low peripheral parasitemia due to the sequestration of the parasite in the placenta [35]. Although microscopy is still considered to be the reference test for the diagnostic of malaria, despite the limit of detection [17], it is unfortunately not readily available in rural areas for reasons such as the lack of qualified staff and sufficient laboratory infrastructure. This is also the case for molecular biology for which specific equipment and highly trained technicians are needed in order to be adequately performed [19]. In order to propose an alternative diagnostic tool for the correct diagnosis of malaria in endemic areas particularly in pregnant women and where suitable laboratory facilities are lacking, an innovative diagnostic platform combining direct blood amplification in a miniaturized PCR system with NALFIA as a read-out to diagnose *Plasmodium* infections in a multiplex format has been developed.

The present trial has been designed to assess the diagnostic performance of this platform for the detection of *Plasmodium* species in pregnant women during antenatal consultation and treatment follow-up. The proposed trial will validate the anticipated low limit of detection and sensitivity and specificity of the new diagnostic platform. If these diagnostic parameters are achieved, this study will provide the evidence needed for the introduction of the mini-dbPCR-NALFIA in the routine health system for a correct diagnosis of malaria and treatment follow-up during pregnancy.

**Trial status:** This is the protocol Version 2.0, of 11 March 2021. Ethical approvals have been obtained for both participating countries. At the time of this manuscript submission, study participants’ enrollment has started in Burkina Faso (8 November 2021), and in DRC (7 December 2021). The trial is ongoing with an anticipated completion date in December 2023.

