#### 2.2.7. Outcomes

The outcome (for the diagnostic screening and treatment follow-up parts) will be reported according to STARD principles [30]. We will report sensitivity, specificity, negative, and positive predictive values (primary outcome) of the mini-dbPCR-NALFIA test. The outcomes of the evaluations will be further analysed using 2 × 2 tables (at 95% confidence intervals), and comparisons of the performance of the diagnostic test under investigation will be made with standard diagnostic procedures in place and qPCR as the accepted reference test to determine the agreement between different tests (expressed as kappa values) [29]. 

To determine the utility of the mini-dbPCR-NALFIA test in monitoring treatment efficacy, parasite clearance will be assessed by mini-dbPCR-NALFIA and compared with qPCR. 

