### 2.6. Statistical Methods

#### 2.6.1. Statistical Methods for Primary and Secondary Outcomes

As mentioned above, the outcomes of the evaluations will be analysed using 2 × 2 tables (at 95% confidence intervals), and comparisons will be made with standard diagnostic procedures in place and qPCR as the accepted reference test. Positive and Negative Predictive Values will be calculated. The sensitivity and specificity of the mini-dbPCR-NALFIA are assumed to be at least 90% [23]. The utility of the mini-dbPCR-NALFIA to monitor treatment success (in terms of recurrent parasitemia) will be compared to qPCR. The association between the molecular test results obtained during the follow-up will be assessed using logistic regression models.

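### The Discussion lets per-test sensitivity and specificity support use for treatment follow-up, but recurrence is a per-woman event read from about eight serial tests, to which per-test specificity does not carry over

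*Protocol article*

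**What the plan says.** Section 2.2.7 (Outcomes) opens by covering both the screening and the follow-up parts, then states: "We will report sensitivity, specificity, negative, and positive predictive values (primary outcome) of the mini-dbPCR-NALFIA test". A separate paragraph there adds that, for monitoring treatment, "parasite clearance will be assessed by mini-dbPCR-NALFIA and compared with qPCR".

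Section 2.6.1 states that "The sensitivity and specificity of the mini-dbPCR-NALFIA are assumed to be at least 90" per cent. It also says "The utility of the mini-dbPCR-NALFIA to monitor treatment success (in terms of recurrent parasitemia) will be compared to qPCR", and gives one model for the follow-up data: "The association between the molecular test results obtained during the follow-up will be assessed using logistic regression models".

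Section 2 (Design/Methods) schedules follow-up samples on days 1, 2, 3, 7, 14, 21, 28, 35, 42, 49-56 and 63. Section 2.2.9 expects about 138 women in follow-up. Section 2.6.4 handles missing data visit by visit and says that a missed visit leaves the analysis of the woman's other visits unaffected.

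The Discussion says the trial will validate the anticipated limit of detection, sensitivity and specificity, and continues: "If these diagnostic parameters are achieved, this study will provide the evidence needed for the introduction of the mini-dbPCR-NALFIA in the routine health system". The rest of that sentence names both correct diagnosis and follow-up of treatment in pregnancy.

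**The concern.** Sensitivity and specificity per sample suit screening, where each woman is tested once. Clearance and recurrence differ in kind, because each is derived from a series of results in one woman. A false-positive rate that is tolerable for one test can become a large false-recurrence rate over eight.

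The Discussion nevertheless gives a single condition for both uses, and no per-woman result is part of it. The trial could find per-sample specificity near its assumed value, conclude that the test is suitable for monitoring treatment, and not know what share of the recurrences called by the test were false. The logistic regression would not reveal this. Two sets of results can be strongly associated while the tests disagree about which women recurred.

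**Working it through.** **Inputs from the protocol article.** Specificity of at least 90% (2.6.1). Eleven follow-up visits, eight of them from day 7 to day 63, counting 49-56 as one visit (section 2). About 138 women in follow-up (2.2.9).

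**Inputs assumed here, not stated in the article.** Any single positive from day 7 on counts as recurrence. Within-woman correlation of errors (ICC) runs from 0 to 0.9. For scale only, 10% of women truly recur and 90% of recurrences are detected.

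**1. Where the 90% fits.** The only planning figure that can be reproduced is the screening sample size of 555. With p = 0.90, prevalence 25% and a half-width of 0.05 (not stated in the article), n = 1.96² × 0.90 × 0.10 / 0.05² = 138.3 infected women. Then 138.3 / 0.25 = 553, or 139 / 0.25 = 556 after rounding up. That is close to 555, so 90% behaves as a design value for single-test screening. No performance figure specific to follow-up is stated.

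**2. Chance of at least one false positive over eight visits, in a woman qPCR-negative at all of them.** With independent errors this is 1 − sp⁸. With correlated errors a beta-binomial is used, with a + b = 1/ICC − 1 and a = (1 − sp)(a + b), so that P(at least one) = 1 − B(a, b + 8)/B(a, b).

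| Specificity | ICC | P(at least one) |
|---|---|---|
| 90% | 0 | 1 − 0.9⁸ = 57.0% |
| 90% | 0.1 | 46.3% |
| 90% | 0.3 | 33.1% |
| 90% | 0.5 | 24.4% |
| 90% | 0.7 | 17.8% |
| 90% | 0.9 | 12.4% |
| 95% | 0 | 33.7% |
| 98% | 0 | 14.9% |
| 99% | 0 | 7.7% |

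At 90% specificity with independent errors, seven visits (starting at day 14) give 52.2%, and nine visits (days 49 and 56 separate) give 61.3%.

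**3. Specificity needed per test.** To hold the per-woman false-recurrence rate at 10% with independent errors, specificity must be 0.9^(1/8) = 98.7%.

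**4. Effect of the rule.** Requiring two consecutive positives at 90% specificity gives 6.3% with independent errors and about 12% at ICC 0.5 (simulated). The choice of rule therefore matters as much as the specificity.

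**5. Scale in this trial.** If 10% of 138 women recur, about 14 do and 138 × 0.9 = 124 do not. Under the single-positive rule at 90% specificity, about 124 × 0.570 = 71 of the 124 would be flagged with independent errors, and about 124 × 0.244 = 30 at ICC 0.5. At 99% specificity with independent errors it would be about 124 × 0.077 = 10. The per-woman positive predictive value is then 0.09 / (0.09 + 0.9 × 0.570) = 15%, 0.09 / (0.09 + 0.9 × 0.244) = 29% and 0.09 / (0.09 + 0.9 × 0.077) = 56%.

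**The case against.** A reader might infer three stronger things that the article does not support.

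- **That follow-up is judged only by per-sample accuracy.** It is not. Sections 2.2.7 and 2.6.1 both plan comparisons with qPCR, for clearance and for recurrent parasitaemia. What they leave open is the unit and the rule, and a full protocol or analysis plan could define these. Their absence from the article is not the fault.
- **That 90% is a pass mark.** Section 2.6.1 calls it an assumption, and the Discussion gives no threshold. The link between the two is an inference from the Discussion's reference to anticipated values, for which the article offers no other figure for sensitivity and specificity.
- **That a test meeting the stated figure would wrongly flag a quarter to over half of cured women.** The figure is at least 90%, and a test with 99% specificity also meets it. The range further needs a single-positive rule, which the article does not state, and an ICC no higher than 0.5. Stronger correlation or a confirmation rule brings it below a quarter.

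It can also be said that this concerns a secondary objective, that index-test results do not guide care (section 2), and that per-woman tables can still be made from the planned samples.

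These limits on wording and size all stand. They do not remove the point, because the Discussion's inference from per-test accuracy to treatment follow-up is stated in the article and is unsound as written. The planned comparisons would not repair it while the claim does not rest on them and the only model given measures association.

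**Conclusion.** The point holds in a conditional form. Achieved per-test sensitivity and specificity would not by themselves support introducing the test for treatment follow-up. At the 90% floor, if any single positive counts, up to about 57% of women who stay qPCR-negative from day 7 to day 63 could be flagged at least once with independent errors, and about 24% at ICC 0.5. At 99% specificity with independent errors the figure is about 8%. The rule and the correlation are assumptions of this review. The direction is more secure than the size: at 90% specificity under this rule, even an ICC of 0.9 leaves 12.4%, above the 10% that the per-test figure suggests.

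This should be changed, but it affects the monitoring conclusion only. Sensitivity and specificity remain the right measures for the screening part.

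**What to change.** **Section 2.6.1.** Derive clearance and recurrence per woman for each test, by a stated rule, and cross-classify the index test against qPCR over the whole follow-up. Report, each with a 95% confidence interval:
- the proportion of women without recurrence by qPCR who have any recurrence by the index test;
- the proportion of qPCR recurrences that the index test detects;
- the difference between the tests in first negative visit.

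Use all follow-up women who are qPCR-positive at baseline. Report those who are index-negative at baseline separately and do not exclude them, since conditioning on a positive index test would remove its own misses and flatter it. Add a sensitivity analysis that requires two consecutive positive index results. It should not be the main analysis, because it can miss a recurrence that ends before the next visit.

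**Discussion.** Limit the per-sample sensitivity and specificity criterion to screening, and rest any claim about treatment follow-up on the per-woman results.

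**Cost.** This is a change of analysis and wording, with no added visits or samples. The per-woman figures will look less favourable than the per-sample ones. Per-woman sensitivity will be imprecise: with about 14 recurrences (10% of 138, assumed), detecting 13 gives an exact 95% interval from 66% to nearly 100%. The false-recurrence proportion is better estimated. With 124 women and a true value of 57%, the half-width is 1.96 × √(0.57 × 0.43 / 124), about 9 percentage points.

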## Data Availability

Final trial outcomes will be published in Open Access peer reviewed journals. Anonymized datasets generated and analyzed during this study will be available for up to 5 years after completion of the project upon a reasonable motivated request to the corresponding author.

## Abbreviations

ACT	Artemisinin Combination Therapy
AMC	Academic Medical Centre
CRF	Case Report Form
CRUN	Clinical Research Unit of Nanoro
DRC	Demographic Republic of Congo
dbPCR-NALFIA	direct-on-blood PCR
DNA	Deoxyribonucleic Acid
eCRF	Electronic Case Report Form
EDCTP	European & Developing Countries Clinical Trials Partnership
EDTA	ethylenediaminetetraacetic acid
HRP2	histidine-rich protein 2
HIV	Human Immunodeficiency Virus
IRSS	Institut de Recherche en Sciences de la Santé
LoD	Limit of detection
NALFIA	Nucleic Acid Lateral Flow Immunoassay
[n]PoC	near Point-of-Care
*P. falciparum*	*Plasmodium falciparum*
PCR	polymerase chain reaction
*Pf*HRP2	*Plasmodium falciparum* histidine-rich protein 2
*p*LDH	*Plasmodium* lactate dehydrogenase
PoC	Point-of-care
QC	Quality Control
qPCR	quantitative PCR
RDTs	Rapid Diagnostic Test
STARD	Standards for Reporting of Diagnostic Accuracy Studies
TDR	Special Programme for Research and Training in Tropical Diseases
UV	ultra violet
WBC	white blood cells
WHO	World Health Organization
